### Statistical considerations

To test the univariate association between depression at 28 days and return to work status at 12 months, a chi-squared test will be conducted. Assuming a conservative prevalence of depression of 25% and an overall return to work of 50% (as found in the ARCOS study[2]), then to detect a relative risk of returning work of 0.5 amongst the depressed we will require 150 participants. We will aim to recruit 220 participants to allow for loss to follow up, potential clustering effects, missing data and to provide sufficient numbers for multivariate modelling. We intend to examine return to paid and unpaid work separately so require a total sample of 440 participants.

### Statistical analysis

We will conduct a logistic regression model with 'returned to work' as a dichotomous response variable and a combination of *a priori *and univariately associated variables described in the 'assessments and data collection' as explanatory variables. The associations with the continuous outcome of the number of quality hours of work returned to will be modelled using linear regression.

The time of first return to work will be modelled by all the other explanatory variables using a Cox regression (survival analysis) model. These models will be fitted on two subsets of data: paid and unpaid work. The same predictor variables will be tested in each model and coefficients in the models for paid and unpaid work will be compared in relation to their size and significance to see how different variables affect return to paid and unpaid work, and time to return to paid and unpaid work.

Economic hardship will be constructed as a dichotomous variable where a reported inability to make any one of the payments posed to respondents will be classed as a case of economic hardship. A logistic regression model will be fitted to determine the extent to which variables affect the risk of this outcome as outlined above. Estimates of average production losses associated with cases of stroke, and stroke with depression as a complication, will be estimated based on an analysis of average amounts of time off work multiplied at the various rates for estimating production gains/losses outlined above. Adjustment for production losses caused by return to work at impaired capacity will be estimated. A sensitivity analysis will be conducted on this economic outcome involving the differing valuation methods and scenarios regarding the level of impairment and its impact on production.

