## Methods/design

### Design and overview

POISE is a prospective multicentre observational study with study registration number ACTRN12608000459325. The primary aim of POISE is to determine if modifiable early (within 28 days of stroke) psychosocial factors are associated with people's ability to return to work one year after stroke. The secondary aim is to determine the economic impact of not returning to work for younger stroke survivors and their families. Participants are recruited as soon as possible after stroke from the Stroke Services New South Wales (SSNSW) network. Stroke status is verified by the recruiting centre staff and baseline demographic and clinical data are collected. Interviews are conducted by centrally located trained interviews at 28 days, 6 and 12 months.

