### Assessments and data collection

The detailed schedule for data collection is shown in Table 1.

**Table 1 T1:** Schedule of assessments in the POISE study

**Participant Assessment ^a^**	**Screening**	**28 days^ b^**	**6 month**	**12 month**
Initials	X			

Date of birth	X			

Sex	X			

Inclusion criteria	X			

Contact information	X			

*Interview Characteristics*				

Method of assessment		X	X	X

Participant or proxy		X	X	X

Alive at scheduled time of assessment		X	X	X

Telephone Interview for Cognitive Status (TICS)[31]		X	X	X

*Demographic characteristics*				

Born in Australia		X		

Years lived in Australia		X		

Language other than English spoken at home		X		

Marital status		X		

Number of financially dependent children		X		

Social/financial living status		X	X	X

Height/Weight		X		

Highest educational qualification		X		

Pre-stroke social activities (Frenchay Activities Index)[32]		X		

*Pre-stroke Medical History*				

Smoking status		X		

Alcohol consumption: Audit Alcohol Use Disorders Identification Test (AUDIT-C)[33]		X		

Activity restricting illness		X		

Comorbidities		X		

Psychotropic medications		X		

Participated in talking therapy for mood		X		

*Current Medical History*				

Psychotropic medications			X	X

Participated in talking therapy for mood			X	X

*Pre-stroke Work Status*				

Lifetime occupation		X		

Most recent occupation		X		

Duration of most recent job		X		

Main income earner		X		

Union/organisation member		X		

Own own business		X		

Hours of paid, unpaid, domestic & volunteer work^c^		X		

Mode of travel to work		X		

Legally able to drive		X		

Drive for work		X		

Modified Job Content Questionnaire (JCQ)[35]		X		

Student		X		

*Current Work Status*				

Want to return to work		X	X	X

Returned to work: part time, full time		X	X	X

Returned to work: same conditions, altered conditions		X	X	X

Hours of paid, unpaid, domestic & volunteer work^c^		X	X	X

Legally able to drive		X	X	X

Mode of travel to work		X	X	X

Advised to stop driving since stroke		X	X	X

Driving since stroke		X	X	X

Student		X	X	X

*Pre-stroke household economics*				

Dependent on other household member for ADL		X		

Received carer payment		X		

Experiencing financial hardship		X		

Received financial assistance to meet costs		X		

Received government benefits		X		

Private health insurance		X		

Income protection insurance		X		

Household weekly income		X		

*Post-stroke household economics*				

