## Discussion

This study addresses a key National Research Priority (ageing well, ageing productively) for a common disabling disease for young Australians. Support for those coping with the aftermath of stroke has been repeatedly stated as a major deficit of current stroke services, and a high priority for consumers. Research in the psychosocial aspects of stroke recovery fills a large gap identified by the National Stroke Foundation Rehabilitation and Recovery Guidelines[40] endorsed by the National Health and Medical Research Council of Australia in 2005.

It is anticipated that this study will, for the first time, reliably identify targets for early intervention and vocational rehabilitation strategies that will increase the proportion of younger stroke survivors who are able to return to a gainful work, here in Australia and internationally. Improving this outcome is considered of primary importance to younger stroke survivors, clinicians and policy makers and may have substantial economic benefits, quantified within this study, and direct implications for the long term psychosocial wellbeing of the many thousands of younger stroke survivors, and their families. An important feature of this study is the quantification of the social and economic consequences of stroke for the individual, society and the global economy, and identification of the key targets for intervention strategies to mitigate these effects.

This study has already generated academic and clinical interest, and support and involvement from health professionals and stroke survivors.

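### The joint regression adjusts the 28-day psychosocial factors for one another, and no described analysis estimates any of them adjusted only for preceding confounders

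*Protocol article*

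**What the plan says.** All references are to the protocol article.

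- **Aim.** Design and overview: "The primary aim of POISE is to determine if modifiable early (within 28 days of stroke) psychosocial factors are associated" with return to work at one year. The Discussion states the use to be made of the results: to "reliably identify targets for early intervention and vocational rehabilitation strategies".
- **Main model.** Statistical analysis: "We will conduct a logistic regression model with 'returned to work' as a dichotomous response variable". The predictors are a mix of unnamed a priori variables and "univariately associated variables described in the 'assessments and data collection' as explanatory variables".
- **Time to return.** Same section: "The time of first return to work will be modelled by all the other explanatory variables using a Cox regression" model.
- **Paid and unpaid work.** The models are fitted to each in turn. "The same predictor variables will be tested in each model", and coefficients are compared on size and significance to show how the variables affect return.
- **Candidate predictors.** Table 1 marks all of these at the 28-day interview: HADS (depression and anxiety), SF-36 vitality, the sleep and daytime tiredness items, WHODAS, perceived social support, and "Want to return to work".
- **Separate test of depression.** Statistical considerations plans a chi-squared test of 28-day depression against 12-month return to work, and sizes the study on it: "to detect a relative risk of returning work of 0.5 amongst the depressed we will require 150 participants".

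**The concern.** Variables are chosen partly by their association with the outcome. Nothing in the rule separates a confounder of a factor from a consequence of it. Fatigue, poor sleep, reduced participation and a lost wish to work are plausible expressions or results of depression, and all are recorded in the same call. If they enter the model, the depression coefficient describes people who differ in depression but are alike in fatigue, sleep, disability and motivation. Whatever part of the depression effect runs through those variables is removed.

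That does not suit a study looking for intervention targets, where the question is what might change if the factor changed, consequences included. The same applies to every other candidate target in the model. A null joint coefficient could lead to a factor being set aside that does affect return to work.

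The motivating result in the Australasian data section is of a different kind. It was adjusted for stroke severity and other potential confounders, and its GHQ-28 was the only psychosocial measure available at 28 days. A null from the joint model here could look like a contradiction of that result when it estimates a different quantity.

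**Working it through.** **1. The plan's own figure.** Inputs from Statistical considerations: 25% depressed, 50% overall return, relative risk 0.5, 150 participants. Alpha, sidedness and power are not stated.

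- Return in the non-depressed: 0.5 / (0.75 + 0.25 × 0.5) = 0.5 / 0.875 = 0.571. In the depressed: 0.286.
- Odds ratio: (0.286/0.714) / (0.571/0.429) = 0.40 / 1.333 = 0.30.
- Depressed group size for a two-sided 5% test, 80% power, 1:3 allocation: [1.96 √((4/3) × 0.5 × 0.5) + 0.842 √(0.286 × 0.714 + 0.571 × 0.429 / 3)]² / 0.286² = (1.132 + 0.450)² / 0.0816 = 30.6, rounded up to 31. Total 4 × 31 = 124. For 90% power the total is 164.
- With 150 the power is 87.6%; with 220 it is 96.8%.
- If 50% is taken as the non-depressed rate, 80% power needs 156, and 150 gives 78.4%.

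So 150 is plausible, though it cannot be checked strictly without alpha and power. It applies to the unadjusted contrast.

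**2. What adjustment does.** Logistic simulation, 600 runs per setting, with the total depression effect calibrated to 25% depressed, 50% return and relative risk 0.5. Four further 28-day variables are added. Two inputs are assumptions, since the article gives neither: their correlation with depression (0.3, 0.5 and 0.7) and the share of the depression effect that runs through them. No confounding is simulated. Ranges are across the three correlations.

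| Share through the four variables | Power, n = 150 | Power, n = 220 | Median OR, n = 220 |
|---|---|---|---|
| Not adjusted for them | 85-88% | 95-98% | about 0.30 |
| Adjusted, none | 66-80% | 76-91% | about 0.29 |
| Adjusted, 30% | 33-51% | 52-70% | about 0.41 |
| Adjusted, half | 21-30% | 28-44% | about 0.53 |
| Adjusted, 70% | 10-16% | 12-22% | about 0.67 |
| Adjusted, all | 4-5% | 5-6% | about 1.0 |

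Monte Carlo standard error is at most √(0.25/600) = 2 percentage points. Rough check of the half row: if half the log odds ratio remains, the OR is √0.30 = 0.55.

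The 220 is a recruitment target that already allows for loss to follow-up and missing data, so the number analysed may lie between the two columns.

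**3. What a given share means.** On the log-odds scale the total effect is |ln 0.30| = 1.20. Four measures, each shifted 0.6 SD in the depressed with log OR 0.1 per SD, carry 4 × 0.6 × 0.1 = 0.24, or 20% of it. Shifted 1.0 SD with log OR 0.3, they carry 4 × 1.0 × 0.3 = 1.2, the whole of it. Both sets of inputs are assumptions; they show only how the share is made up.

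**4. Which estimates the plan would yield.**

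| Estimate | Depression | Other psychosocial factors |
|---|---|---|
| Crude | Chi-squared test | Univariate screen; no separate estimate described |
| Adjusted for preceding confounders only | Not described | Not described |
| Mutually adjusted | Joint model, if it enters | Joint model, if it enters |

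**The case against.** **No covariates are named.** A reader might infer that vitality, sleep, WHODAS and the wish to return are all forced in beside depression. The article does not say so: an item enters if it is a priori or passes the screen, and the list may be fixed in a fuller document. This stands. The selection rule and the reading of coefficients as effects are stated, however, and the rule favours items related to the outcome. The background section on psychosocial predictors already names ADL dependency among the most consistent predictors.

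**Depression is tested on its own.** A reader might infer that a depression effect of the size planned for would go unseen. It would not: the chi-squared test addresses it directly, with about 88% power at 150. This stands and narrows the point. The test is not adjusted for stroke severity and covers depression only.

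**Early disability may be a confounder.** WHODAS covers self-care and mobility. Disability could lower mood and also prevent return, so omitting it could exaggerate depression. All items come from one interview, so their order is unknown. This stands, and it is why neither version should be shown alone.

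**The aim speaks of association.** Mutual adjustment is a conventional way to find independent predictors. That is fair for a descriptive aim. The Statistical analysis and Discussion sections go further, to effects and targets.

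**The power loss follows from the assumptions.** This also stands. With none of the effect mediated the OR does not move, and only precision is lost.

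**Conclusion.** The concern holds in a limited form. The plan as described offers a crude result for depression and a mutually adjusted result for whichever factors enter. It describes no estimate adjusted for preceding confounders alone, for depression or any other candidate target, although that is the estimate closest to the stated use.

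The size cannot be fixed from the article. With 220 analysed and four correlated companion variables held fixed, power for depression could be anywhere from 76-91% (none mediated) to 5-6% (all mediated), against 95-98% without them. These figures rest on assumed correlations and mediation shares and on the absence of confounding. They show what could happen and are not a forecast. No simulation was run for the Cox model; the same reasoning applies to it.

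The documents do not support the stronger reading that depression will be adjusted away, nor that every companion variable is a consequence of it. The change is worth making because it is cheap and affects how the main results are read.

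**What to change.** - For each modifiable 28-day psychosocial factor, add a logistic and a Cox model adjusted for one fixed set of preceding confounders: age, sex, stroke severity and subtype, education, pre-stroke work and pre-stroke mood treatment. All are already collected. Report these beside the joint model.
- Show each factor's estimate with and without WHODAS, because early disability may be a confounder or a pathway.
- State that joint-model coefficients are conditional associations, and that a null there alone does not rule a factor out as a target.

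**Cost.** A few extra models and some wording, with no new data. Estimates for correlated factors share effects and must not be added together. The version without WHODAS may carry residual confounding by early disability. The separate models do not show which of several overlapping factors matters independently, so the joint model stays.

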### The importance of psychosocial predictors of return to work

There is a paucity of information on potentially modifiable psychosocial predictors of return to work after stroke, especially in comparison with other cardiovascular diseases.[12] Studies of return to work following myocardial infarction have consistently found that psychosocial factors are important predictors.[11] In contrast, psychosocial factors have been considered in only a few stroke studies, where white collar workers[13] and those with higher education levels were found to be more likely to return to work in general,[11] and those with less demanding roles more likely to return after adjusting for stroke severity.[14] The most consistent predictors of return to work after stroke have been stroke severity (not modifiable) and dependency in activities of daily living (ADL).[11]

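### Univariate screening and an uncapped Cox covariate set, drawn from a pool not expressly limited to pre-stroke and 28-day values, leave about 1.3 to 2.1 events per variable on a literal reading

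*Protocol article*

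**What the plan says.** The Statistical analysis section of the protocol article sets two covariate rules.

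- **Logistic model for return to work (yes/no):** explanatory variables are some named in advance together with "univariately associated variables described in the" assessments section.
- **Cox model:** "The time of first return to work will be modelled by all the other explanatory variables using a Cox regression" (survival) model.

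The models are fitted separately for paid and unpaid work. The section says the predictors are common to the models, and that paid and unpaid coefficients are compared on magnitude and statistical significance. It gives no list, selection threshold or cap.

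The section named as the source contains Table 1. That table includes a block on current work status, with items such as "Want to return to work", at 28 days, 6 months and 12 months. The accompanying text adds that the date of return is recorded. The primary aim, in Design and overview, concerns psychosocial factors measured within 28 days.

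Under Statistical considerations the size is set as follows: "Assuming a conservative prevalence of depression of 25% and an overall return to work of 50" per cent, "to detect a relative risk of returning work of 0.5 amongst the depressed we will require 150 participants". Then: "We will aim to recruit 220 participants to allow for loss to follow up, potential clustering effects, missing data" and to support multivariable modelling. Finally: "We intend to examine return to paid and unpaid work separately so require a total sample of 440 participants".

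**The concern.** Choosing covariates by their association with the outcome in the data then used to fit the model is a weak rule. It keeps noise variables that happen to correlate with the outcome and can drop confounders not named in advance. It also gives intervals and p-values that ignore the selection. Entering a large set without regard to the number of events makes Cox estimates unstable and Wald tests too liberal.

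The pool adds a second risk. It holds items that are post-stroke work status, or that are measured at or near the time of the outcome. Such items would be expected to pass a screen against return to work, and adjusting for them could remove part of the effect of an early psychosocial factor.

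The study's product is a list of modifiable targets for early intervention, which the Discussion expects to be reliable. False targets, and a depression effect either over-adjusted or left confounded, go directly against that purpose.

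**Working it through.** **The plan's own figure.** With 25% depressed, 50% returning overall and a relative risk of 0.5, return in the non-depressed is 0.50 / (0.25 × 0.5 + 0.75) = 57.1%, and in the depressed 28.6%. Alpha, sidedness and power are not stated, so 150 cannot be reproduced uniquely. At two-sided 5% without continuity correction the need is 124 for 80% power and 164 for 90%, and 150 participants give 87.6%. The figure is plausible and is not disputed. It is, however, the requirement for a univariate chi-squared test.

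**Events per work type.**
- 150 × 0.50 = 75, if the allowance for loss, clustering and missing data is used up.
- 220 × 0.50 = 110, if nobody is lost.

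The article takes 50% from an earlier study that assessed paid work only. Using it for unpaid work is an assumption.

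**Candidates (count of Table 1).** Rows marked at 28 days: interview 4, demographic 9, pre-stroke medical 6, pre-stroke work 12, current work 9, pre-stroke economics 8, post-stroke economics 2, disability 1, mood 1, sleep and vitality 3, rehabilitation 1, social contacts 3, overall 1. Total 60. Removing the three interview-administration rows and the nine current-work rows, and adding age, sex, stroke subtype and severity, gives 60 − 3 − 9 + 4 = 52.

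**Events per variable, literal reading of the Cox sentence, one parameter per item.**

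| Events | 60 items | 52 items |
|---|---|---|
| 75 | 1.25 | 1.44 |
| 110 | 1.83 | 2.12 |

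The range is about 1.3 to 2.1, before multi-category items add parameters. Even if all 440 contributed to one model with no loss, 220/52 = 4.2.

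**What such a Cox model does.** Simulation with independent predictors, all truly unrelated to the outcome, 100 data sets each, share of 5% Wald tests that reject:
- 150 participants, 57 predictors (60 rows less the three administrative ones): about 17%
- 220 participants, 52 predictors: about 11%
- 150 participants, 8 predictors: about 5.5%

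These rates are approximate; separate runs of the first case ranged from 14% to 17%. At 17%, 57 null predictors give 57 × 0.17 = 9.7 false positives on average, against 57 × 0.05 = 2.9 at the nominal rate.

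**What the screen does.** The document gives no threshold; 5% is assumed here, with 50 unrelated candidates. On average 50 × 0.05 = 2.5 pass. With independent candidates the chance that at least one passes is 1 − 0.95^50 = 92%; with pairwise correlation 0.2 it is about 86%. After refitting the logistic model on those that pass (600 data sets), the share of final models with at least one falsely significant predictor is:

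| Participants | Independent | Correlation 0.2 |
|---|---|---|
| 150 | 88% | 58% |
| 220 | 90% | 58% |

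The larger sample does not help, because the screen's error rate does not depend on sample size. These simulations treat every candidate as null, so they show how noise variables behave and do not forecast the study's results.

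**The case against.** The strongest reply is that the Cox sentence does not mean every row of Table 1. The preceding paragraph has just defined the explanatory variables as those named in advance plus those passing the screen, and the section goes on to say that the predictors are common to the models. On that reading Cox uses the logistic set, and neither the 1.3 to 2.1 nor the 57- and 52-predictor simulations apply. This stands: the ratio depends on the literal reading. It does not remove the screening problem, which then passes into the Cox model. It also leaves a tension, since screening within two subsets would normally produce two different sets.

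Other parts of the reply also stand.

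- Univariate association is not the only route. Variables named in advance enter whatever the screen shows, so a confounder on that list is protected. Which variables these are is detail for a fuller document, and its absence here is no fault.
- A reader might infer that the outcome itself, or 12-month measures, will be used as predictors. The documents do not support that. Return to work is named as the response, and the primary aim ties the factors of interest to 28 days. The fair point is only that the named pool contains these items and the covariate rule does not exclude them.
- Desire to return to work, asked at the same 28-day interview as mood, could be a psychosocial factor of interest rather than an intermediate. The document does not fix a causal order.
- The target of 220 is meant partly to support modelling, so 75 events is the low end and not the plan's figure.

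**Conclusion.** The concern holds in limited form. The article fixes outcome-driven univariate screening as one route into the logistic model, and a Cox covariate set with no cap, drawn from a pool with no express limit to pre-stroke and 28-day values. This is a stated method, so a later plan that followed it would carry it forward.

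The size depends on the reading. Literally, the Cox model has about 1.3 to 2.1 events per variable, assuming 50% return in each work type, 150 to 220 participants and one parameter per item. If Cox reuses the logistic set, no ratio can be calculated and the defect is the screening alone. In simulation with a 5% threshold and 50 unrelated candidates, that put a falsely significant predictor in 58% to 90% of final models.

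The change should be made before analysis. It does not call the data collection or the sample size for the univariate test into question.

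**What to change.** Reword the Statistical analysis section.

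1. Drop the univariate screen.
2. Fix one adjustment set of pre-stroke and 28-day variables in advance, sized to the events. An example is age, sex, stroke severity and subtype, pre-stroke comorbidity, pre-stroke mood treatment, education, and pre-stroke occupation or hours. Prior knowledge to build it exists, since the Background itself says that "The most consistent predictors of return to work after stroke have been stroke severity" and dependency in daily activities.
3. Use the same set in the logistic, linear and Cox models and for both paid and unpaid work. Add each 28-day psychosocial factor to it.
4. State that post-stroke work status and all 6- and 12-month measures are excluded as predictors. Decide in advance whether 28-day desire to return to work is a factor of interest or an intermediate.
5. Label any wider search exploratory.

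On size: the eight example items, with two parameters for the three stroke subtypes and one for each other item, plus one psychosocial factor, make 10 parameters. That gives 75/10 = 7.5 to 110/10 = 11 events per parameter. Other defensible sets exist; what matters is that the set is fixed beforehand and is small enough for the events.

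The cost is wording only, with no new data. The downside is that fewer factors are mutually adjusted at once.
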